#### Subject withdrawal criteria

2.3.3

Subjects will be able to voluntarily withdraw from the study at any time. Upon removal of a subject from the study, laboratory and clinical evaluations that would otherwise have been obtained upon completion of the study will be obtained where possible. In the case of subjects removed due to an AE, the patients will continue to receive medical care and remain under observation by the attending physician for as long as deemed appropriate.

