#### Sample size

2.8.1

The sample size estimation was based on the mean difference in the change of the OM intensity from baseline. Based on a previous study, we made the following assumptions in calculating the sample size: a mean difference of 0.9 between the two groups, SD of total score of 0.7, a ratio of 1:1 between the two groups, a two-sided significance level of 0.025 and a power of 0.9 [10]. With these assumptions, a minimum sample size of 34 patients (17 patients in each group) is needed. Considering the estimated 15% dropout rate, the estimated sample size is 40 patients (20 patients per group).

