#### Data analyses

2.8.2

All statistical analyses will be performed by qualified statisticians in SPSS software (SPSS Inc., Chicago, IL, USA; version 13.0) based on the intention to treat (ITT) principle. The data will also be collected and analyzed according to said principle. Continuous variables will be expressed as mean ± SD and compared using unpaired independent *t* tests. Chi-square tests will be used to compare the categorical data between groups.

A two-sided *p* < 0.05 will be considered significant. The trends of change over time in degree of OM, each scale/item of the EORTC QLQ-H&N35 and EORTC QLQ-C30, will be compared between groups with the generalized estimating equation (GEE) in SAS software version 9.4.

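### VAS pain, a primary outcome, is left out of the planned GEE and so has only an unpaired t test, which drops anyone without a value at the visit tested

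*Protocol article*

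**What the plan says.** Section 2.8.2 states that all analyses are "based on the intention to treat (ITT) principle". It assigns unpaired t tests to continuous variables and chi-square tests to categorical ones. It then lists what is followed over time: the degree of OM and each scale or item of the two EORTC questionnaires are "compared between groups with the generalized estimating equation (GEE) in SAS software version 9.4". Pain on the 100-mm VAS is not in that list, although the abstract and 2.7.1 make it a primary outcome and 2.7 schedules outcome assessments from t0 to t8.

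On loss of patients, 2.8.1 says "Considering the estimated 15% dropout rate, the estimated sample size is 40 patients (20 patients per group"; the rate is used only to inflate the sample size. Section 2.3.3 says that for removed subjects "laboratory and clinical evaluations that would otherwise have been obtained upon completion of the study will be obtained where possible". Section 1 says that OM can interrupt cancer treatment and lower compliance. Section 2.7.3 allows a participant to be withdrawn because of an adverse event of either the anti-cancer treatment or the herbal product.

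**The concern.** As written, pain at a given visit is compared only among patients who have a pain score at that visit. Scores from earlier weeks, which would show that a patient was doing badly before leaving, are not used.

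This matters if loss depends on how bad the mucositis is, and more so if it does so differently by arm. The article gives reasons to expect the first and to allow for the second: OM affects compliance, adverse events can lead to withdrawal, and adverse events of the herbal product can arise only in the ZYLGS arm. The late comparison could then understate a real effect. It could also show a difference where there is none, either against ZYLGS (if the worst control patients leave) or in its favour (if the worst ZYLGS patients leave).

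**Working it through.** **The plan's own figures.** Inputs from 2.8.1: the effect and spread are given as "a mean difference of 0.9 between the two groups, SD of total score of 0.7". Allocation is equal. The calculation uses a two-sided alpha of 0.025 with 90% power.

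- Normal approximation: n = 2 × (2.241 + 1.282)² × (0.7/0.9)² = 2 × 12.41 × 0.605 = 15.0, which the routine used rounds up to 16 per arm.
- Exact t calculation: 17 per arm, power 0.913. This is the article's 34.
- Dropout: 34 / 0.85 = 40, as stated.

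The sample size reproduces. The 15% enters the plan nowhere else.

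**Size of the shift by hand.** If a fraction p of an arm is lost, and the lost patients would have scored δ above that arm's full mean, the observed mean moves by −δ × p/(1 − p). With p = 0.15 the multiplier is 0.15/0.85 = 0.176. If the other arm's loss is unrelated to severity, that shift is the bias in the arm difference.

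**Simulation.** It uses the OM-grade scale, because the article gives an SD for that scale and none for VAS. Taken from the article: SD 0.7, true difference 0.90 or 0, loss 15%. Assumed: 7 visits; control mean rising from 0.3 to 2.4; within-patient correlation exchangeable 0.6 or AR(1) 0.8; loss after weeks 3 to 5 with logit P(loss) = a + 2 × last observed grade, and a set to give 15%. In the one-arm-only rows, each arm loses 15% but the other arm's loss is unrelated to grade. Large samples are used so that bias, not noise, is seen. Benefit is control minus ZYLGS at the last visit.

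| Loss driven by severity in | True benefit | Observed-case benefit | Bias |
|---|---|---|---|
| both arms, same rule | 0 | 0 | none |
| both arms, same rule | 0.90 | 0.84 to 0.85 | about −0.05 to −0.06 |
| control arm only | 0 | about −0.07 to −0.08 | against ZYLGS |
| ZYLGS arm only | 0 | about +0.07 to +0.08 | favours ZYLGS |

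By the hand formula, 0.07 to 0.08 corresponds to δ = 0.07/0.176 to 0.08/0.176, or about 0.40 to 0.45 grade: the lost patients would have ended about 0.6 SD worse than their arm's average.

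**Sensitivity.** With an odds ratio of 4 per grade (exchangeable 0.6) instead of e² ≈ 7.4, the one-arm shift is about 0.06; at an odds ratio of 2 it is about 0.03. With AR(1) 0.9 and log-odds 2 it reaches about 0.10. Opposite mechanisms in the two arms (odds ratio 4 in one, 0.25 in the other) give 0.12.

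**Against the standard error.** SE = 0.7 × √(2/n).

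- n = 17 per arm (2.8.1): SE 0.240, so 0.07 to 0.08 is about 0.3 SE.
- n = 85 per arm (the abstract's 200, less 15%, halved): SE 0.107, so it is about 0.65 to 0.75 SE.

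**The GEE on the same data.** With an exchangeable working correlation it came within about 0.01 of the truth in these scenarios, including those where the true correlation was AR(1). With independence working correlation and visit as a category it equals the observed-case result.

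**The case against.** The strongest reply is that a condensed article need not state how missing data are handled, and that nothing in 2.8.2 says observed-case, completers only or no imputation. That stands for the GEE: its working correlation, weighting and missing-data assumption may be in a fuller document. It stands less well for pain, because the article does fix a method for continuous variables, and it lists the outcomes for repeated-measures analysis without including this one.

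A reader might go further and infer that the named methods as a whole are biased, or that they contradict the ITT promise. The documents do not support either. No working correlation is stated, and an ordinary choice removes nearly all the bias in the scenarios tested. A t test or a GEE can serve an ITT analysis. Replacing the GEE for OM grade by a mixed model would be a preference.

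A reader might also infer that every patient who drops out has no late score, or that a removal evaluation will be entered as an end-of-RT value. Section 2.3.3 plans to recover evaluations where it can, interrupted treatment is not in itself a missing outcome, and nothing says how a removal evaluation will be slotted. The second worry is speculation.

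It is also fair that no section states that loss will differ by arm, that log-odds of 2 per grade is a strong mechanism, and that the simulation was run on OM grade and not on VAS.

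The rule in 2.6 that excludes ZYLGS patients taking under 70% of their medication does sit badly with ITT and those passages must be reconciled, but that is a separate point.

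**Conclusion.** The point holds in a limited form. A primary outcome has been given the one named method that ignores the earlier visits, in a trial that itself expects "Considering the estimated 15% dropout rate" to matter. The plausible bias is modest: about 0.07 to 0.08 grade, or 0.10 to 0.11 SD (0.07/0.7 and 0.08/0.7), in either direction, if severity-driven loss is confined to one arm. It is nil under no effect when the rule is common to both arms. It matters little at 17 per arm and more at 85.

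These sizes rest on an assumed dropout mechanism and correlation. Carrying them to VAS pain assumes similar behaviour in SD units. This is a worthwhile improvement to a stated method; it does not show that the trial's comparison is invalid.

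**What to change.** In 2.8.2:

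- Analyse VAS pain with a repeated-measures model (arm, visit, arm by visit) using every observed visit of every randomised patient. Either a likelihood-based mixed model or the GEE already planned for OM grade would do, the latter with a non-independence working correlation or inverse-probability-of-remaining weights.
- Take the end-of-RT arm difference in pain from that model, and in OM grade from the GEE, and not from single-visit t tests.
- Keep the GEE for OM grade, but state that an independence working correlation will not be used without weights.
- State that an evaluation made at removal is entered at the week it was taken.

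The cost is a change of wording and one further analysis in the SAS software already named, with no new data. The downside is slightly more modelling and reliance on a missing-at-random assumption, which the data cannot confirm.

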#### Data collection and management

2.8.3

All data will be recorded on the case report form (CRF) and stored anonymously in laboratory computer at the KCGMH. Investigators will provide access to data files based on reasonable requests. The researcher is ultimately responsible for collecting and reporting all applicable data entered into the CRF in a timely manner, and ensuring that they are accurate, original, attributable, complete, legible, and available when needed.

## Discussion

3

RT-induced OM is a common problem and one of the major causes of pain and functional incapacity in HNC patients [3]. The present study aims to assess the effects of our TCM preparation on prevention and management of the pain, severity, and QoL of HNC patients with OM.

Many CHMs show significant improvements in side effects related to anti-cancer treatment, and TCM is the most common means of CIM in Taiwan. In a previous nationwide cohort study in Taiwan, 12.6% of patients with HNC used CIM, and the authors found that the number of TCM visits increased during multiple cancer treatments [22]. Another study reported the utilization of TCM to improve the survival outcome for HNC, and the results showed that longer use was associated with lower mortality [23]. We believe that it is possible to select formulae based on the pathogenesis of RT-induced OM and to use TCM theory to reduce the side effects of cancer treatment.

According to TCM theory, RT is a type of heat toxin that damages *qi* and yin and gradually affects the patient's physical strength [13]. Chemotherapy is also considered to aggravate a lack of *qi* [24], which can make wound healing more difficult [25]. ZYLGS provides an attractive therapeutic option for the prevention and management of OM, for the concept of using herbal components to clean the heat, replenish *qi* and nourish yin has been recorded in classical TCM books. Modern pharmacological research shows that *Rx. Scutellariae*, *Rx. Glycyrrhizae* and *Hb. Menthae Haplocalycis* have positive effects on oral epithelial damage. Their mechanism may be to inhibit oxidative stress and inflammation and thereby prevent bacterial dysbiosis [14]. *Hb. Dendrobii* can modulate macrophage activity via the NF-kB pathway and has been shown to act as an immune modulator to regulate gastrointestinal mucosal barrier function [26,27]. *Rx. Ophiopogonis* has been reported to stimulate lymphocyte proliferation *in vitro* [28]. Both are used for the benefit of *qi* and to promote body fluid production, according to TCM theory, and they are also reported to have the effects of cardiovascular protection, anti-inflammation and anti-cancer [27,29,30]. Although *in vitro* and *in vivo* studies have provided evidence supporting the purported effects of these ingredients of ZYLGS, we still perceive a need for a clinical trial to assess the efficacy of CHM formula in treating RT-induced OM.

Each medication in the ZYLGS formula is described in the ancient TCM literature as relatively safe, and in previous meta-analyses, therapeutic doses have been found to cause no significant toxicity in cancer patients [31,32]. However, some serious adverse reactions have been reported from time to time in recent years. For example, it has been reported that prolonged use or overdose of *Rx. Glycyrrhizae* leads to pseudohyperaldosteronism such as hypertension, hypokalemia or metabolic alkalosis, with low serum aldosterone levels [33]. For potential immunoallergic reactions, such as those associated with *Rx. Scutellariae*, which has liver [34] and lung toxicity [35], attention should also be paid to the safe range of medicine usage, the dosage should not be excessive, and the processed products should be selected appropriately according to needs. Despite their sourcing from TCM pharmaceutical factories in Taiwan with Good Manufacturing Practices certification, the safety and herb–drug interactions and toxicity must be monitored.

Our study has some limitations. One is that the research is being conducted in a single center with a small sample size. Second, the study is not a double-blind trial. Third, only short-term observations can be made, so this study cannot produce a long-term prognosis. For example, it will not be possible to predict whether the reduction of side effects of CHM formula will affect the RT cytotoxic effect and thus affect the survival rate.

In conclusion, we have proposed a randomized controlled, open-label, single-center trial to evaluate the efficacy and safety of ZYLGS as a CIM therapy for RT-induced OM. The results of the current research will provide high-quality evidence for assessment of the prophylaxis of RT-induced OM using a TCM-based prescription of ZYLGS.

## Trial registration

Clinicaltrials.gov registry (NCT05040425), registered 03 September 2021; Pre-results.

## Data Availability

Data will be made available on request.
